#### A6. Expected outcomes or impacts of research

| A6.1 What is the potential significance of this project for improved health outcomes? | |
| --- | --- |
|  | Evidence exists showing that high-volume LIET benefits fitness, health, and exercise adherence but this form of traditional training is usually undertaken by a narrow band of healthy participants of average or above average fitness. There is a paucity of evidence available to demonstrate whether traditional programs are appropriate for the wider community. Therefore, there is a clear need to examine outcomes and adherence to alternative exercise programmes such as a high intensity (low volume) exercise prescription. The potential benefits include decreased risk of developing cardiovascular disease and diabetes in at risk subjects, decreased risk of developing complications in those with pre-existing disease and improved quality of life. |
|  | |
| A6.2 What is the potential significance of this project for the advancement of knowledge? | |
|  | Peak aerobic fitness has been shown to be the strongest independent predictor of mortality compared with other established risk factors in healthy and unhealthy subjects. Previous research has found that HIIT improves aerobic fitness more than LIET. Moreover, interval training results in superior improvements in insulin signalling (in fat and muscle) and skeletal muscle biogenesis as well as reducing blood glucose levels and lipogenesis in adipocytes. It has also been found that HIIT can also benefit remodelling of heart muscle. However, prominent researchers examining this new exercise paradigm have stressed the need for further research with a wider range of populations. In addition, this knowledge needs to be applied to community-based interventions. Only through such research will it be possible to develop evidence-based alternatives to traditional time intensive high-volume exercise prescriptions for non-athletic populations. |
|  | |
| A6.3 What steps will be taken to disseminate the research results? | |
|  | A report will be prepared for the sponsors (DHB translational research fund, HRC). In addition, results of the project will be presented at various forums including national and international conferences and local seminars. Finally a number of peer-reviewed research articles will be prepared from the results of this project.  Study results will be fed back to local participants in a group setting, under the guidance of local Maori leaders. |

#### A7. Publication of results

| Will any restriction be placed on publication of results? | |  | Yes | X | No |
| --- | --- | --- | --- | --- | --- |
|  | | | | | |
| If **yes**, please supply details. |  | | | | |

#### A8. Funding

| A8.1 How will the project be funded? | | | | | |
| --- | --- | --- | --- | --- | --- |
|  | Funding for the main project has been granted through the 2009 Translational Research funding round, Health Research Council of New Zealand’s District Health Board Research Fund.  Separate funding will be sought for consumables for the mitochondrial depletion sub study (estimated cost $20,000). | | | | |
|  | | | | | |
| A8.2 Does the researcher, the host department, the host institution or the | |  | Yes | X | No |
| locality organisation have any conflict of interest, eg, financial interest, in the outcome of this research? If **yes**, please give details. | | | | | |
|  |  | | | | |

#### A9. Incentive payments

| A9.1 Have you read and understood the description of incentive payments in the | | X | Yes |  | No |
| --- | --- | --- | --- | --- | --- |
| Guidelines? | | | | | |
| **Note: Details about any payment (in money or kind) or reward made to participants recruited into the project are to be provided in question E10.** | | | | | |
|  | | | | | |
| A9.2 Does the funding available to the project depend upon the number of participants | |  | Yes | X | No |
| recruited, eg, is the funding on a per participant basis?. If **yes**, give details of the amount per participant. Where there is a significant difference between these, this incentive to recruit should be declared in the information sheet. | | | | | |
|  |  | | | | |
|  | | | | | |
| A9.3 Does the funding available to the project include any form of incentive (in money | |  | Yes | X | No |
| or kind) for the early or complete recruitment of a specified number of participants, eg, bonus payments to the researcher, host department or host institution? If **yes**, give details. | | | | | |
|  |  | | | | |
|  | | | | | |
| A9.4 Will **all** funding available to the project be passed through an audited research | | X | Yes |  | No |
| account or cost centre? If **yes**, give details. If **no**, specify why not. | | | | | |
|  | The project is registered with the Research Office, Christchurch Hospital. They will advise about the setting up of a Cost Centre, to ensure that funds are disbursed through an appropriate mechanism that will stand up to audit. | | | | |

## *B. Minimisation of harm (Operational standard p*aragraphs 60–68)

| B1. How many visits/admissions of participants will this study involve? Clarify what is in addition to standard treatment. Give also an estimate of total time involved for participants. | | | | | | | | | | | | |
| --- | --- | --- | --- | --- | --- | --- | --- | --- | --- | --- | --- | --- |
|  | **Phase 1:** In addition to the prescribed exercise sessions three times a week for <50 minutes, over 12 weeks (ie the intervention), participants will be required to attend one visit for consent, a fasting visit before and after completion of the study for fasting venesection and a non fasting visit to the exercise laboratory, before and after the completion of the study, for fitness testing and anthropomorphic measurements. Each of these 5 additional visits will take less than one hour.  **Phase 2:** The exercise treatment (ie intervention) for this phase is one supervised exercise training session and two unsupervised training sessions per week of up to 50 minutes duration per session, over a period of six months. After the consenting visit, subjects will attend for fasting venesection at weeks 0, 13 and 26 and attend the exercise laboratory for fitness testing and anthropomorphic measurements on a separate day at weeks 0, 13 and 26. Each of these 7 additional visits will take less than one hour. | | | | | | | | | | | |
|  | | | | | | | | | | | | |
| B2. Who will carry out the research procedures? | | | | | | | | | | | | |
|  | Venesection will be undertaken by trained researchers, including research nurses. Collection of anthropometric measurements will be undertaken by all researchers, under the supervision of [name], who is Level II accredited with the **International Society for the Advancement of Kinanthropometry (ISAK).**  Clinical assessments will be undertaken by the research nurses, under the supervision of [name] and also directly by [name]. [name] will be responsible for screening potential subjects’ medical fitness to participate in the project, in conjunction with a report from the subject’s General Practitioner, as required.  Exercise testing (ie measurement of V02max) will be undertaken by trained exercise physiology researchers – [name], [name], [name], [name]. The exercise interventions will be supervised either directly by these exercise physiologists, or indirectly through supervision of exercise physiology students, who will undertake the assessment. | | | | | | | | | | | |
|  | | | | | | | | | | | | |
| B3. What other research studies is the lead investigator currently involved with? | | | | | | | | | | | | |
|  | [name] will have completed data collection for a three year HRC funded dietary study, by December 2009. She supervises sample collection on behalf of the Christchurch Diabetes Centre, for TrialNet, a long term multinational natural history study of antibody status of subjects at risk of type 1 diabetes. She is the Diabetes Centre site investigator for two international pharmaceutical studies of DPP IV inhibitors (an efficacy and a cardiovascular outcome study). | | | | | | | | | | | |
|  | | | | | | | | | | | | |
| B4. Where will the research procedures take place? | | | | | | | | | | | | |
|  | Fasting venous blood samples and questionnaires will collected at Christchurch Diabetes Centre.  Anthropometric and Exercise testing will take place at the Exercise Science Laboratory, University of Canterbury ([name] Campus).  Exercise training will take place in a local park (e.g. Hagley Park) | | | | | | | | | | | |
|  | | | | | | | | | | | | |
| B5. How do the research procedures differ from standard treatment procedures? | | | | | | | | | | | | |
|  | Overweight subjects at risk of developing diabetes and cardiovascular disease do not usually have ‘free’ access to an exercise programme and fitness testing. The exercise programme and fitness testing will however follow a standardised protocol, which is similar to that undertaken by sports medicine physicians. Subjects will undergo venesection and complete questionnaires. | | | | | | | | | | | |
|  | | | | | | | | | | | | |
| B6. What are the benefits to research participants of taking part in the project? | | | | | | | | | | | | |
|  | Participants will benefit by learning about their own health and wellbeing. They are also likely to benefit by becoming healthier through a combination of physiological changes that occur following the introduction of regular exercise (e.g. weight loss, reduced blood pressure, improved lipid profile and lipid composition, increased insulin sensitivity). | | | | | | | | | | | |
|  | | | | | | | | | | | | |
| B7. Describe any methods for obtaining information. Attach questionnaires and interview guidelines. (If National Health Index (NHI) information is used, see the Guidelines (NAFG-2009-v1).) | | | | | | | | | | | | |
|  | Participants anthropometric and fitness data will be measured using standard tests and procedures. Information will also be gained via standard metabolic measurements (anthropomorphic measurements and blood tests). We will also gain information via the following validated, published questionnaires (see attachments).  Four questionnaires will be used. They are: 1. Four day prospectively collected food record, 2. Quality of Life questionnaire (SF36) 3. Fitness to exercise PAR-Q questionnaire and 4. readiness to change questionnaire. | | | | | | | | | | | |
|  | | | | | | | | | | | | |
| B8. Briefly describe the inclusion/exclusion criteria and include the relevant page number(s) of the protocol or investigator’s brochure. | | | | | | | | | | | | |
|  | **Inclusion Criteria:**  Aged 35-60 years inclusive  BMI ≥28 and ≤40  Sedentary (no regular physical activity in last 3 months).  **Exclusion Criteria:**  Underlying musculoskeletal conditions that preclude subjects being able to walk briskly for up to 50 minutes  Active cardiac conditions including angina  Intermittent claudication  Underlying respiratory conditions, including asthma requiring use of an inhaler within the previous one year  Any chronic condition which, in the opinion of the potential subject’s GP or principle investigator, would make it unsafe for the subject to participate in a high intensity exercise programme (ie brisk walking)  Myopathy, including subjects on statins with moderate to severe myopathic symptoms  Active psychiatric illness  Any other chronic condition that might require a change in medication during the study (for example subjects with diabetes on sulphonylureas and insulin, subjects requiring variable doses of oral corticosteroids)  Pregnant or planning to become pregnant during the duration of the study  History of malignancy (other than skin malignancy excluding melanoma) in the previous 5 years  Treated hypertension requiring more than one antihypertensive agent  Current or recent weight change (self reported) of >5kg in last 3 months  Other reasons why taking part would be practically difficult | | | | | | | | | | | |
|  | | | | | | | | | | | | |
| B9. What are the physical or psychological risks or side effects to participants or third parties? Describe what action will be taken to minimise any such risks or side effects. | | | | | | | | | | | | |
|  | **Physical risks to participants.** The PAR-Qquestionnaire will be used to screen for higher risk participants with pre-existing minor health problems. Those with positive answers to health questions will be monitored more closely. As with any exercise programme, there is a risk of musculoskeletal injury but this will be minimised by subjects undertaking supervised warm-up exercises beforehand. Physical risks include unmasking of underlying asymptomatic cardiovascular problems during the fitness tests when participants will be asked to go up to their maximum exercise level. Physical risks will be minimised by strictly following exercise protocols. Trained individuals from either an exercise physiology or nursing/medical background with the relevant first aid qualifications will be available during the supervised exercise sessions. Appropriate emergency equipment and standardised emergency procedures are available at the exercise physiology laboratory.  **Psychological risks to participants.** There include anxiety prior to and during venesection and when completing fitness and anthropometric tests. Psychological risks associated with the fitness and anthropometric tests will be minimised by a variety of methods. These include undergoing fitness testing in secluded rooms away from other participants, receiving an explanation about the testing procedures and what is expected of the participants before starting the exercise testing. | | | | | | | | | | | |
|  | | | | | | | | | | | | |
| B10. What facilities/procedures and personnel are there for dealing with emergencies? | | | | | | | | | | | | |
|  | Venepucture will be undertaken by trained personnel ie research nurses and doctors, who are experienced in minimising and treating any adverse reaction associated with venepuncture, such as a vaso-vagal reaction (fainting). During exercise testing (to be undertaken at the University of Canterbury campus), the following staff/equipment will be present; a registered nurse, more than 3 people in the testing room at any time at least one of which will have current first aid certificate, defibrillator, direct line to campus Security, direct line to hospital. In addition, Security will be advised that the project is taking place in case of emergencies. | | | | | | | | | | | |
|  | | | | | | | | | | | | |
| B11. What arrangements will be made for monitoring and detecting adverse outcomes? | | | | | | | | | | | | |
|  | 1. **Exercise programme.** The direct supervisors of the exercise programme will ask participants to report minor (as well as major) physical symptoms, such as musculoskeletal pains. These adverse events will then report back to the research nurse and physician ([name]). A course of action as a result of symptoms may be suggested e.g. a rest/recovery period away from exercise for minor musculoskeletal pains. Alternatively the participant may be advised to seek an opinion from their GP for more serious complains. 2. **Exercise testing.** Some subjects may suffer transient light headedness of breathlessness during maximal exercise testing. If this progresses, the exercise test will be terminated early. Participants will be observed for any adverse outcomes during the course of their exercise testing. After exercise testing participants will be monitored for at least 20 minutes. Exercise physiologists or their students will also be in regular contact with participants, as they will be supervising the regular exercise sessions. 3. **Venesection.** No major adverse events are anticipated but there may be minor bruising that will be minimised by applying pressure to the venepuncture site. Subjects with a history of vasovagal faints will be venesected lying down. | | | | | | | | | | | |
|  | | | | | | | | | | | | |
| B12. If the study is a clinical trial, are participants to be provided with a card | | | | | |  | Yes | | X | | No | |
| confirming their participation, medication and the contact phone number of the principal investigator? No, because they are not on any study medication | | | | | | | | | | | | |
|  | | | | | | | | | | | | |
| B12.1 Do you intend to inform the participant’s GP that their patient is a | | | | | | x | Yes | |  | | No | |
| participant in this study? (If yes, consent from the participant is required.) | | | | | | | | | | | | |
|  | | | | | | | | | | | | |
| B12.2 Do you intend to inform the GP of all clinically significant abnormal | | | | | | X | Yes | |  | | No | |
| results obtained during study conduct? | | | | | | | | | | | | |
|  | | | | | | | | | | | | |
| B13. Is the trial being reviewed by a data and safety monitoring board (DSMB)? | | | | | |  | Yes | | X | | No | |
|  | | | | | | | | | | | | |
| If **yes**, who is the funder of the DSMB? | | | |  | HRC |  | Sponsor | |  | | Other | |
|  | | | | | | | | | | | | |
| If **‘Other’**, please specify. | | Not applicable | | | | | | | | | | |
|  | | | | | | | | | | | | |
| B14. What are the criteria for terminating the study? | | | | | | | | | | | | |
|  | For individual participants, all adverse reactions will be reviewed by the research nurse and physician and advice may also be sought from the participant’s GP. Any of these health professionals may choose to terminate an individual’s involvement with the study, on medical grounds.  There are no-preset endpoints for terminating the study for protocol related reasons. | | | | | | | | | | | |
|  | | | | | | | | | | | | |
| B15. Will participants be exposed to any potential toxins, mutagens or | | | | | |  | Yes | | X | | No | |
| teratogens? | | | | | | | | | | | | |
| If **yes**, specify and outline the justification for their use. | |  | | | | | | | | | | |
|  | | | | | | | | | | | | |
| B16. Will any radiation or radioactive substances be used? | | | | | | |  | Yes | | X | | No |
| **Note: If any form of radiation is being used, please answer B16.1–B16.2. If no, go to question B17.** | | | | | | | | | | | | |
| B16.1 How many x-rays or other procedures are planned for the purposes of this study, ie, that are not part of standard treatment? | | |  | | | | | | | | | |
|  | | | | | | | | | | | | |
| B16.2 Under whose licence is the radiation being used? | | |  | | | | | | | | | |
|  | | | | | | | | | | | | |
| B16.3 Has the National Radiation Laboratory (NRL) risk assessment | | | | | | |  | Yes | |  | | No |
| Been completed? | | | | | | | | | | | | |
| If **yes**, please enclose a copy of the risk assessment and a contact name and phone number.  If **no**, please explain why not. | | |  | | | | | | | | | |
|  | | | | | | | | | | | | |
| B17. Will any medicines be administered for the purposes of this study? | | | | | | |  | Yes | | X | | No |
|  | | | | | | | | | | | | |
| B17.1 If **yes,** is Standing Committee on Therapeutic Trials (SCOTT) | | | | | | |  | Yes | |  | | No |
| approval required? | | | | | | | | | | | | |
| B17.2 Has SCOTT approval been given? (Please attach.) | | | | | | |  | Yes | |  | | No |
|  | | | | | | | | | | | | |
| B18. Does the study involve the use of health care resources? | | | | | | |  | Yes | | x | | No |
| If **yes**, please specify: | | | | | | | | | | | | |
|  | There is no direct use of health care resources. This study is sponsored by the DHB as part of a DHB/HRC translational funding grant. We will be utilising Diabetes Centre premises mainly outside clinic hours (early morning and weekends) and we will not be compromising clinical activities. CHL laboratory costs are fully funded as part of the study agreement. | | | | | | | | | | | |
|  | | | | | | | | | | | | |
| B19. What effect will this use of resources have on waiting list times for patients, that is, for diagnostic tests or for standard treatments? | | | | | | | | | | | | |
|  | Nil | | | | | | | | | | | |

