**Key:**

Randomisation and group allocation, timetable details finalised for exercise groups

Fasting venesection, anthropomorphic measurements

and questionnaires

Exercise treadmill testing - measurement of VO2 max

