**Baseline Testing**

About a week prior to baseline testing, consenting subjects will be sent a four day food record and instructions about completing this, the quality of life and health and exercise history questionnaires and the facilitators and barriers to change questionnaire. They will also be given instructions about undertaking an overnight fast. Subjects will bring their completed questionnaires to the first study visit.

Day -1. Arrive at Diabetes Clinic ([name]) from 7am-9am in fasted state.

Hand in completed records and questionnaires, which will be checked for completeness by the researchers. Any outstanding issues with the consent forms will be completed prior to venesection. A

fasting blood sample will be taken and anthropomorphic measurements will also be done in the fasting state. Subjects will be offered a light breakfast, as required and any outstanding paperwork will then be completed.

It is anticipated that up to 10 subjects will be screened on any given morning.

Day 0. Arrive at Canterbury University (College of Education Exercise laboratory, [name]) between 7am-10am either fasting or after a light breakfast (subject’s preference). Complete Maximal Treadmill Test.

Facilities and staff are available to undertake testing in up to twelve subjects per morning.

Days 2-14. Rest – await results of randomisation and group allocation.

Days 2-14 Start the exercise programme within a fortnight of randomisation.

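### Section B and Appendix 1 give different visits, places and fed states for anthropometry, and Appendix 1 does not hold a participant's fed state constant between VO2max tests

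*Protocol*

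**What the plan says.** **Anthropometry, Section B.** For Phase 1, B1 describes "a non fasting visit to the exercise laboratory, before and after the completion of the study, for fitness testing and anthropomorphic measurements", separate from the fasting blood visit. For Phase 2, B1 has participants "attend the exercise laboratory for fitness testing and anthropomorphic measurements on a separate day at weeks 0, 13 and 26", again apart from venesection; it does not restate the fed state there. B4 gives the place: "Anthropometric and Exercise testing will take place at the Exercise Science Laboratory, University of Canterbury".

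**Anthropometry, Appendix 1.** Under Baseline Testing, Day -1 takes place at the Diabetes Clinic, where a "fasting blood sample will be taken and anthropomorphic measurements will also be done in the fasting state". The key to the Phase 1 study outline groups the items in the same way, "Fasting venesection, anthropomorphic measurements", with the treadmill test as a separate entry. The closing Phase 2 text of Appendix 1 says the measurements follow Phase 1 and that only the exercise venue changes, so the fasting Diabetes Centre visit carries over to weeks 0, 13 and 26.

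**Treadmill test.** On Day 0, Appendix 1 has participants arrive at the university laboratory between 7 and 10 am "either fasting or after a light breakfast", as they prefer. Post Testing repeats the baseline schedule after 12 weeks. It does not say that a participant must repeat the baseline choice.

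**What depends on this.** Variables to be Measured (Appendix 1) lists weight, waist and bioimpedance under anthropometry. A5.2 makes change in VO2max primary, changes in BMI and waist secondary, and change in % body fat tertiary.

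**The concern.** The two accounts of anthropometry differ on visit, building and fed state. Both cannot be followed unless everything is measured twice, which the protocol nowhere says. Each outcome is a change within a person, so a difference in scale, impedance device or recent food and drink between two visits goes straight into the outcome. B2 has all researchers collecting anthropometry, under one accredited supervisor, and testing is split over two places, so it is plausible that different people would work from different sections. With 16 completers per arm expected in Phase 1 and 22 in Phase 2 (A4.1), avoidable measurement noise is unwelcome.

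The treadmill point is different in kind. It needs no slip by staff: Appendix 1, followed exactly, allows one participant to be fasted at one VO2max test and fed at the next.

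**Working it through.** The protocol states no figure on this point, so there is none to reproduce. The check is a comparison of sections, then a rough scale.

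**Step 1. Anthropometry, side by side**

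| Source | Visit | Place | Fed state |
|---|---|---|---|
| B1, Phase 1 | with fitness testing | exercise laboratory | non-fasting |
| B1, Phase 2 | with fitness testing, not on the venesection day | exercise laboratory | not restated |
| B4 | with exercise testing | exercise laboratory | not stated |
| Appendix 1, Baseline Testing | with blood sampling, Day -1 | Diabetes Centre | fasting |
| Appendix 1, outline key | with fasting venesection | not stated | fasting, by grouping |
| Appendix 1, closing Phase 2 text | as Phase 1 | as Phase 1 | as Phase 1 |

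Section B and Appendix 1 conflict on visit and place in both phases, and on fed state explicitly in Phase 1.

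**Step 2. Does either account mix conditions by itself?** No. B1 applies one arrangement both before and after the Phase 1 programme, and Post Testing in Appendix 1 repeats the baseline schedule. Mixing arises only if one section is used at one visit and the other at another.

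**Step 3. Scale for BMI.** Assumptions, not in the protocol: height 1.70 m, and a fed weighing heavier than a fasted one by d = 0.5 to 1.0 kg.

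Shift in BMI = d / height², with 1.70² = 2.89 m².

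- d = 0.5: 0.5 / 2.89 = 0.17 kg/m2
- d = 1.0: 1.0 / 2.89 = 0.35 kg/m2

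This is the shift in one person's change score when the two visits differ in fed state. The protocol gives no standard deviation for BMI change, so it cannot be converted to a loss of power. It also gives nothing from which to size the effect of a meal on waist or bioimpedance.

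**Step 4. Scale for VO2max through body weight.** Inputs: untrained VO2max of 30 ml/kg/min and a Phase 1 detectable difference of about 4 (A4.2); the BMI limits of 28 and 40 (B8); the same assumed height and d.

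Weights: 28 × 2.89 = 80.92 kg; 40 × 2.89 = 115.6 kg.

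With oxygen uptake in absolute terms unchanged, dividing by a weight lower by d gives a shift of 30 × w / (w − d) − 30.

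| w (kg) | d = 0.5 kg | d = 1.0 kg |
|---|---|---|
| 80.92 | 0.19 | 0.38 |
| 115.6 | 0.13 | 0.26 |

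The range is 0.13 to 0.38 ml/kg/min. Against 4, that is 0.13 / 4 = 3% to 0.38 / 4 = 9.5%. Any direct effect of a meal on treadmill performance is not covered by this sum, and the protocol gives no figure for it.

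**The case against.** The best defence is that no section plans mixed anthropometry, and that A3.1 sends the reader to Appendix 1 for more detail, so staff would naturally work from Appendix 1 throughout. The first part stands: a reader might infer that the protocol itself builds in different conditions before and after, and for anthropometry it does not. The second part is weaker. Pointing to further detail does not make Appendix 1 override Section B, and B4 is the direct answer on where procedures take place.

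A reader might also infer that Section B and Appendix 1 contradict each other on the fed state for the treadmill test. That is not firm. B1 answers a question about the number and length of visits, and its description can mean that fasting is not required, which is compatible with the choice in Appendix 1. What remains is that the choice is not held constant. The 7 to 10 am window already limits variation in time of day.

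A third inference would be a biased treatment comparison. Nothing in the protocol ties place or fed state to arm, and A5.2 compares randomised groups by ANCOVA with the baseline value as covariate. Mixing unrelated to arm adds variance; a shift in one person's BMI is not a shift in the treatment effect.

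Nor should the primary outcome be called seriously exposed. The weight effect is small, and it may not arise at all if the fasting weight from the day before is the divisor. The respiratory exchange ratio is recorded during the test but is not among the outcomes listed in A5.2, so it adds nothing here.

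**Conclusion.** The point holds in a limited form. The schedule for anthropometry is contradictory in the current text on visit and place in both phases, and on fed state explicitly in Phase 1. The exposure is extra noise in two secondary outcomes and one tertiary outcome, and only if different sections are followed at different visits. For BMI it is about 0.17 to 0.35 kg/m2 in an affected person, resting on the assumed 0.5 to 1.0 kg and 1.70 m.

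The treadmill rule is a separate, smaller gap that lets fed state vary within a person between tests of the primary outcome. Through body weight it is worth about 0.13 to 0.38 ml/kg/min on the same assumptions, under a tenth of the stated detectable difference in Phase 1. Both are worth correcting because correction is nearly free, not because the trial's main conclusion is at risk.

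**What to change.** Reconcile B1, B4, the outline key, Baseline Testing and the Phase 2 text of Appendix 1 so that all anthropometry, bioimpedance included, has one visit, one place and one fed state, the same at every time point in both phases. Either account would remove the conflict if used throughout. The fasting visit in Appendix 1 is the natural choice, since that is the detailed testing schedule and fasting is the more uniform condition, provided the bioimpedance equipment is available at the Diabetes Centre; the protocol does not say whether it is.

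For the treadmill test, record each participant's fed state at baseline and require the same at each later test.

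Cost: wording, one extra recorded item, less participant choice at follow-up, and possibly moving equipment between the two places. No visit is added.
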